| **Maximum Tolerated Dose (MTD)** | The maximum tolerated dose (MTD) refers to the lower dosage next to a dose with which DLT occurs in 2 or more out of 6 patients during the DLT evaluation window. |
| **Dose-Escalation Phase** | The doses are proposed to be escalated to 0.1 mg/kg, 0.5 mg/kg, 1.0 mg/kg, 1.5 mg/kg, 2.0 mg/kg, 2.5 mg/kg, 3.0 mg/kg, 3.5 mg/kg and 4.0 mg/kg (if the last dose has not yet reached the MTD, it should continue to increase by 0.5 mg/kg).  On Oct. 18, 2016, the investigators and sponsor decided to add a dose-escalation trial with Q3W administration in the dose-escalation phase. Starting from the 2.0 mg/kg dose group, 2-3 patients are enrolled. Pharmacokinetic data from Q3W administration are collected repeatedly. The dose next to 2.0 mg/kg is determined based on the results of the dose escalation study with Q2W administration. The extended trial is started with the 2.0 mg/kg dose group.  On July 4, 2017, the investigators and sponsor decided that: 1) Symptomatic treatment is allowed during the DLT evaluation period. Dose escalation trials are performed in subjects according to the traditional 3+3 mode, wherein doses are proposed to be escalated from 2.5 mg/kg to 3.0 mg/kg, 3.5 mg/kg and 4.0 mg/kg with Q2W administration until MTD is reached, or the sponsor and investigators decide to terminate the escalation study. 2) The original dose-escalation study starting with 2.0 mg/kg Q3W is stopped. Dose escalation trial is carried out with an initial dose of 1.25mg/kg, followed by 1.5mg/kg, in the traditional 3+3 mode with QW administration. Symptomatic supportive treatment is allowed in the DLT evaluation period until MTD is reached. If the 1.5 mg/kg dose group does not reach MTD, the sponsor and investigators will jointly decide on the next escalating doses or whether to terminate the dose escalation trial. |

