**3 Study Design**

It is expected to set up 9 dose groups to conduct an open-label, dose-escalation study. Patients with HER2-positive solid tumors are enrolled.

The doses are proposed to be escalated to 0.1 mg/kg, 0.5 mg/kg, 1.0 mg/kg, 1.5 mg/kg, 2.0 mg/kg, 2.5 mg/kg, 3.0 mg/kg, 3.5 mg/kg and 4.0 mg/kg.

If a dose has passed the safety observations in another Phase I clinical trial (at the Cancer Hospital, Chinese Academy of Medical Sciences), investigators and sponsors may meet to discuss and adjust the dose increment in dose escalation trial, or skip this dose and proceed directly to the next dose according to the corresponding results, in order to reduce the patient's exposure to ineffective doses.

During the trial, the dose increment and the maximum dose can be adjusted based on actual results after consultation between the investigators and sponsor.

The first dose (0.1 mg/kg) is given to 1 subject to collect pharmacokinetic data of a single dose. After safety observations, the patient can continue with trials of the following dose levels on a voluntary basis without additional collection of pharmacokinetic data (this scheme is suitable to all subsequent subjects to ensure their benefits).

The second dose (0.5 mg/kg) group enrolls another subject. Pharmacokinetic data of a single dose are collected for this patient after first dosing. Dosing interval (Q1W, Q2W or Q3W) will be determined by the investigators and sponsor based on the data obtained from the 2 patients. Q2W was tentatively selected at a meeting on Jan. 26, 2016. Q2W dosing means 1 treatment cycle includes 2 doses.

Repeated doses are given to subjects from the second dose (0.5 mg/kg) forward to collect pharmacokinetic data of repeated doses. Pharmacokinetic data are collected before and after each of 4 doses for one patient, no matter what dosing interval is used.

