Subjects are enrolled in the traditional 3+3 mode from the third dose (1.0 mg/kg) forward. At first, 3 qualified subjects are enrolled into the 1.0 mg/kg group. If no DLT is observed in the 3 subjects during the DLT evaluation period, the dose is escalated to the next level; if DLT occurs in 1/3 of the subjects (1 case) in the 1.0 mg/kg group, another 3 subjects should be added. If no DLT is observed in the additional 3 subjects, trials at the next dose level may be started; if DLT occurs in 1 or more of the 3 additional subjects, or in 2 or more of the 6 subjects in total, the dose escalation should be discontinued. Trials in the same manner are performed with dose escalation until the maximum tolerated dose (MTD) and recommended phase Ⅱ dose (RP2D) are determined.

[figure not shown]

All subjects are evaluated as CR, PR or SD after the 4th administration. If the patients are willing to do so, and the investigator determines that continued administration will be of benefit to the patients, patients can enter the extended test in which treatment is continued until the disease progresses, the toxicity become intolerable, the patients withdraw consent or the investigator determines that the medication must be discontinued.

**Dose-limiting toxicity (DLT)** refers to the following toxic reactions observed in the DLT evaluation window (observation period of Day 1-21 after the first dose) that are considered related to RC48-ADC treatment by the investigators or sponsor, wherein the grading is based on the 5-level system of the CTCAE v4.0:

- Grade 4 neutropenia.
- Neutropenic fever (defined as absolute neutrophil count ^[^ANC] < 1000/mm3 accompanied by a fever higher than 38.3 °C or a fever above 38 °C that persists for more than 1 h).
- Grade 3 neutropenia with confirmed infections.
- Grade 3 thrombocytopenia with bleeding tendency.
- Grade 4 thrombocytopenia.
- Non-hematologic toxicity of Grade 3 or higher after supportive care. Except for nausea, vomiting and hair loss.
- Renal toxicity ≥ Grade 3.
- Neurological toxicities ≥ Level 2 that persist until the next administration.
- Cardiac toxicity ≥ Grade 2.
- Hepatic transaminases reach grade 2 at baseline, with a level ≥10×ULN.

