If DLT appears in the subjects, treatment of RC48-ADC should be discontinued first, and adverse reactions should be dealt with actively until the toxicity returns to ≤ Grade 1. Thereafter, medication should proceed at a decreased dose level (specific doses will be determined by the investigators).

**Maximum Tolerated Dose (MTD)**: The lower dosage next to a dose with which DLT occurs in 2 or more out of 6 patients during the DLT evaluation window.

Dose groups of 3 to 6 subjects were formed starting with the lowest dose set by the protocol:

(1) If none of the 3 subjects develop DLT within the 21-day observation period after the first dose, the next (escalated) dose trial can be performed.

(2) If DLT occurs in 1 of the 3 subjects, the number of subjects in this dose group should be increased to 6: (a) if DLT occurs in 2 or more of these 6 subjects, the next (escalated) dose trial should be terminated; (b) if DLT occurrs in no more than 1 of the 6 patients, the next (escalated) dose trial can be performed.

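### The MTD definition does not match the escalation rules: it needs six patients at the toxic dose and sets no data requirement for the dose it names

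*Protocol*

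**What the plan says.** Determining the MTD is a primary objective (Study Summary; section 2). The Study Summary says that the MTD "refers to the lower dosage next to a dose with which DLT occurs in 2 or more out of 6 patients". Section 3 gives the same definition twice, the second time after the July 2017 change to the DLT criteria: "The lower dosage next to a dose with which DLT occurs in 2 or more out of 6 patients during the DLT evaluation window".

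The escalation rules in section 3, described as the traditional 3+3 mode from 1.0 mg/kg upward, are:

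- Go up after 0 of 3: "If none of the 3 subjects develop DLT within the 21-day observation period after the first dose", the next dose can be started.
- Expand after 1 of 3: "If DLT occurs in 1 of the 3 subjects, the number of subjects in this dose group should be increased to 6".
- Go up after at most 1 of 6: "if DLT occurrs in no more than 1 of the 6 patients, the next (escalated) dose trial can be performed".
- Stop if a DLT occurs among the three added subjects, "or in 2 or more of the 6 subjects in total, the dose escalation should be discontinued".

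If a dose has passed safety observations in another Phase I trial, sections 3 and 5 allow the team to "skip this dose and proceed directly to the next dose according to the corresponding results". Both sections also allow dose increments to be adjusted during the trial. Table 1 (section 5) plans 1 subject each at 0.1 and 0.5 mg/kg and 3-6 at each level from 1.0 to 4.0 mg/kg. The QW escalation starts at 1.25 mg/kg (Study Summary; sections 5 and 18).

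**The concern.** The definition and the step rules were written to different outcomes. The definition recognises a toxic dose only by its result among six patients, although a level can fail within its first three. It then takes the dose below without asking how many subjects were treated there, what was seen in them, or whether that dose was given in this trial at all.

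At stake is the result of a primary objective. After a first-cohort failure the written definition yields no MTD. In other cases it can yield one supported by three subjects, by a single enrolled subject, or by another trial's data. Two teams with the same data could name different doses.

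**Working it through.** The protocol states no operating characteristic for its MTD rule, so there is no figure to reproduce. The rules come from section 3 and the group sizes from Table 1. True DLT rates are not given; p = 0.2 to 0.5 per level is my assumption.

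**1. Outcomes at a level, set against the text**

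| Outcome | Step rule | Does the MTD definition recognise a toxic dose? |
|---|---|---|
| 0/3 | next level | not a failure |
| 1/3, then 0/3 (1/6) | next level | not a failure |
| 1/3, then at least 1/3 (2/6 or more) | stop | yes |
| 2/3 or 3/3 | none written | not literally: six were not treated |

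**2. How often the uncovered outcome arises**

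P(2/3 or 3/3) = 3p²(1−p) + p³. P(level cleared) = P(0/3) + P(1/3) × P(0/3), with P(0/3) = (1−p)³ and P(1/3) = 3p(1−p)². P(stop) = 1 − P(cleared), counting 2/3 and 3/3 as stops.

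| p | P(2/3 or 3/3) | P(stop) | Share of stops in the first cohort |
|---|---|---|---|
| 0.2 | 0.096 + 0.008 = 0.104 | 1 − (0.512 + 0.384 × 0.512) = 0.291 | 36% |
| 0.3 | 0.189 + 0.027 = 0.216 | 1 − (0.343 + 0.441 × 0.343) = 0.506 | 43% |
| 0.4 | 0.288 + 0.064 = 0.352 | 1 − (0.216 + 0.432 × 0.216) = 0.691 | 51% |
| 0.5 | 0.375 + 0.125 = 0.500 | 1 − (0.125 + 0.375 × 0.125) = 0.828 | 60% |

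**3. What a cleared level rests on**

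The share of cleared levels that were cleared on 0/3 is 1/(1 + P(1/3)): 72%, 69%, 70% and 73% at the four rates. With no DLT in n subjects, the one-sided 95% upper limit for the DLT rate is 1 − 0.05^(1/n):

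- 0/1: 95%
- 0/3: 1 − 0.05^(1/3) = 63%
- 0/6: 1 − 0.05^(1/6) = 39%
- 1/6 (exact binomial): 58%

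**4. The whole ladder, under four assumed rising DLT curves for 1.0 to 4.0 mg/kg**

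- A: 0.02, 0.05, 0.10, 0.20, 0.35, 0.50, 0.60
- B: 0.05, 0.10, 0.15, 0.25, 0.35, 0.45, 0.55
- C: 0.02, 0.03, 0.05, 0.10, 0.20, 0.30, 0.45
- D: 0.10, 0.20, 0.33, 0.45, 0.55, 0.65, 0.75

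Among trials that stop:

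| Result | A | B | C | D |
|---|---|---|---|---|
| Stop came from 2/3 or 3/3 | 46% | 42% | 42% | 45% |
| Named MTD rests on 0/3 | 76% | 73% | 76% | 67% |
| Named MTD rests on 1/6 | 24% | 24% | 24% | 24% |
| Named MTD is 0.5 mg/kg (one enrolled subject) | 0.5% | 2.7% | 0.5% | 9.4% |
| Of MTDs resting on 0/3: would show at least 2/6 if filled to six | 12% | 11% | 9% | 14% |

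For a single level with p = 0.4, clearance on 0/3 has probability 0.6³ = 0.216, and three more subjects would show at least 2 DLTs in 35% of those cases.

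**5. Which lower dose is meant**

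The text does not say whether the next lower dose is the next one on the planned list or the next one given. If it is the listed one, a skipped level can be named. On the QW schedule the first level is 1.25 mg/kg, so if that level failed the definition would point to no QW dose.

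**The case against.** The best defence is that the definition must be read together with the step rules. From 1.0 mg/kg upward, every level given under 3+3 was cleared in this trial on 0/3 or at most 1/6 before the next one opened. A reader might infer that the MTD uses no data on the dose it names. That is true of the definition sentence only and is not supported by section 3 as a whole.

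Second, a traditional 3+3 ordinarily stops at 2 of 3, and once 2 of 3 have a DLT the condition of 2 or more in six is certain to be met. A figure follows these rules in section 3; it could not be read and may show the branch. This stands: the gap is one of wording, nothing orders three further subjects after 2/3, and the gap does not push the named dose upward. It leaves the definition unmet as written.

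Third, a reader might infer that a skipped level is untested. The skip clause requires that it passed safety observations in another Phase I trial, so it is only a level not given in this trial. The increment-adjustment sentence carries no such condition, but the problem arises only if next lower means the planned list.

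Fourth, a reader might infer that early leavers count as free of DLT, or that subjects moving up ("the patient can continue with trials of the following dose levels on a voluntary basis") count in the next cohort. The protocol says neither; it is silent.

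Fifth, clearing a level on 0/3 is inherent in 3+3, so the limits in step 3 apply to any such design. That is fair, but clearing a level for escalation is a different decision from declaring it the MTD, and this definition sets no standard for the second.

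Finally, at least 30 extension patients are planned at 2.0 mg/kg Q2W, so a recommendation at that dose would not rest on three subjects. The MTD definition does not refer to them, however. Section 10.2 also sets different supportive-treatment rules in the extension from those in the DLT window, so the DLT counts are not directly comparable.

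**Conclusion.** The point holds as a mismatch between the MTD definition and the escalation rules, and it should be corrected. The definition does not cover a level that fails in its first cohort (10% to 50% of cohorts at assumed rates of 0.2 to 0.5). It also lets the MTD rest on 0/3, with an upper limit of 63%. That is the most frequent basis under all four assumed curves, and filling to six would overturn 9% to 14% of those MTDs. All these probabilities depend on assumed DLT rates and on treating 2/3 and 3/3 as stops; the confidence limits do not.

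The single-subject case at 0.5 mg/kg follows from the rules as written, but it arises only if 1.0 mg/kg fails. Section 1.5 reports that escalation had reached 2.5 mg/kg by 1 July 2017, so on the Q2W ladder it is now mainly a point about the text.

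Section 1.5 also reports DLTs in 2 cases at 2.5 mg/kg. A reader might infer that this level had failed and that 2.0 mg/kg was already the MTD. The documents do not settle this: no denominator is given, and the DLT definition was then changed. It does show that the missing denominator matters in practice.

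**What to change.** Reconcile the three statements of the MTD (one in the Study Summary, two in section 3) with the step rules, so that the definition:

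- applies to a level that fails within its first three subjects as well as to one that fails among six, with the first-cohort outcomes of 2/3 and 3/3 written out;
- refers to a level actually given in this trial on the schedule concerned, and says what is reported if no such lower level exists, as below 1.25 mg/kg QW;
- requires the named level to be filled to six and to meet the standard of no more than 1 DLT in 6, already in section 3, rule (2)(b), before it is declared the MTD;
- counts only subjects who had a DLT or were observed through the 21-day window at that level.

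Extension subjects should not be pooled into this count unless the different supportive-treatment rules in section 10.2 are acknowledged.

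The cost is amendment wording and up to three more subjects at one level. From 1.0 to 4.0 mg/kg this stays within the 3-6 in Table 1. Table 1 allows only one subject at 0.5 mg/kg and does not list the QW level of 1.25 mg/kg, so the amendment should state the numbers for those cases.

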**On July 4, 2017, the investigators and sponsor decided to modify the DLT definition based on the current study results:**

**DLT** refers to the following toxic reactions observed in the DLT evaluation window (observation period of Day 1-21 after the first dose) that are considered related to RC48-ADC treatment by the investigators or sponsor, wherein the grading is based on the 5-level system of the CTCAE v4.0:

- Grade 4 neutropenia lasting more than 3 days after symptomatic treatment; or grade 4 neutropenia recurring after recovery to a normal level through symptomatic treatment.
- Neutropenic fever (defined as absolute neutrophil count ^[^ANC] < 1000/mm3 accompanied by a fever higher than 38.3 °C or a fever above 38 °C that persists for more than 1 h).
- Grade 3 neutropenia with confirmed infections.
- Grade 3 thrombocytopenia with bleeding tendency.
- Grade 4 thrombocytopenia.
- Non-hematologic toxicity of Grade 3 or higher after supportive care. Except for nausea, vomiting and hair loss.
- Renal toxicity ≥ Grade 3.
- Neurological toxicities ≥ Level 2 that persist until the next administration.
- Cardiac toxicity ≥ Grade 2.
- Hepatic transaminases reach grade 2 at baseline, with a level ≥10×ULN.

If DLT appears in the subjects, treatment of RC48-ADC should be discontinued first, and adverse reactions should be dealt with actively until the toxicity returns to ≤ Grade 1. Thereafter, medication should proceed at a decreased dose level (specific doses will be determined by the investigators).

**Maximum Tolerated Dose (MTD)**: The lower dosage next to a dose with which DLT occurs in 2 or more out of 6 patients during the DLT evaluation window.

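### In the July 2017 DLT list, a short Grade 4 neutropenia with a low-grade infection and no qualifying fever meets no item, while Grade 3 with the same infection is a DLT

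*Protocol*

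**What the plan says.** Before July 2017, the DLT list in section 3 (Study Design) and in the Study Summary contained the unqualified item "Grade 4 neutropenia" and, separately, Grade 3 neutropenia with a confirmed infection.

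The list modified on July 4, 2017 appears in the Study Summary, in section 3 and in section 18. Its Grade 4 item now begins "Grade 4 neutropenia lasting more than 3 days after symptomatic treatment; or grade 4 neutropenia recurring after recovery to a normal level". The infection item is unchanged: "Grade 3 neutropenia with confirmed infections". Two other items can catch an infected neutropenic subject:
- the neutropenic-fever item, which needs an ANC below 1000/mm3 "accompanied by a fever higher than 38.3 °C or a fever above 38 °C that persists for more than 1 h";
- the item "Non-hematologic toxicity of Grade 3 or higher after supportive care", which exempts only nausea, vomiting and hair loss.

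The 3+3 rule in section 3 runs on the resulting count: "If none of the 3 subjects develop DLT within the 21-day observation period after the first dose, the next (escalated) dose trial can be performed". Two or more DLTs among six subjects stop escalation. Section 10.2 allows G-CSF as treatment, but not as prevention, for Grade 4 neutropenia in the DLT window from July 2017.

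**The concern.** While every Grade 4 neutropenia was a DLT, the infection item needed to name only Grade 3. The amendment removed that cover for short Grade 4 episodes and did not adjust the infection item. In one corner of the list, the deeper neutropenia now scores lower than the shallower one with the same infection.

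The MTD is a primary objective, and the modified list governs the levels still to be tested: 3.0 to 4.0 mg/kg Q2W, and the QW escalation from 1.25 mg/kg. Section 1.5 reports Grade 4 neutropenia as the DLT in 2 cases at 2.5 mg/kg, so this family of toxicity is already known at the edge of the tested range. An event left out can only lower the DLT count, so any resulting error in the MTD points upward.

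**Working it through.** The plan states no figure to reproduce. The check is one of list logic, followed by an illustration.

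**Step 1: does Grade 3 in the infection item mean at least Grade 3?** The same list writes "Renal toxicity ≥ Grade 3" and "Non-hematologic toxicity of Grade 3 or higher after supportive care" where it means at least that grade. It also lists Grade 3 thrombocytopenia with bleeding tendency next to all Grade 4 thrombocytopenia. The neutropenia items had that same structure until July 2017. On the text, the infection item means Grade 3 only.

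**Step 2: score the cases.** Take a drug-related episode with a confirmed infection. If it reaches Grade 4, it lasts 2 days after symptomatic treatment and does not recur. There is no other DLT.

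| Qualifying fever | Infection itself Grade 3 or higher after supportive care | Neutropenia | List before July 2017 | July 2017 list |
|---|---|---|---|---|
| No | No | Grade 3 | DLT | DLT |
| No | No | Grade 4 | DLT | **not a DLT** |
| No | Yes | Grade 3 or 4 | DLT | DLT |
| Yes | No | Grade 3 or 4 | DLT | DLT |
| Yes | Yes | Grade 3 or 4 | DLT | DLT |

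Only one row reverses. In that row, three of three subjects with the Grade 4 event score 0/3 and the next dose may be opened. Three of three with the Grade 3 event would stop escalation.

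**Step 3: effect on the 3+3 rule.** A level passes with 0/3 DLTs, or with 1/3 followed by 0/3:

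P(pass) = (1−p)³ + 3p(1−p)² × (1−p)³

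Let a be the rate of DLTs that the list scores and b the rate of the unscored event, occurring in different subjects. Both are assumptions; the protocol gives neither.

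- a = 0.10, event not counted: 0.9³ + 3(0.10)(0.9⁵) = 0.729 + 0.177 = 0.906.
- a = 0.10, event counted at b = 0.05: 0.85³ + 3(0.15)(0.85⁵) = 0.614 + 0.200 = 0.814. At b = 0.10 it is 0.709, and at b = 0.15 it is 0.600.
- a = 0.20, event not counted: 0.709. Counted at b = 0.05, 0.10 and 0.15: 0.600, 0.494 and 0.396.

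The result can also be expressed as the share of true DLTs that goes unscored, with p replaced by p × (1 − share):

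| True DLT rate | All counted | 1–3% unscored | 10–30% unscored |
|---|---|---|---|
| 0.33 | 0.434 | 0.441–0.454 | 0.500–0.641 |
| 0.25 | 0.600 | 0.605–0.616 | 0.654–0.762 |

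The direction is fixed. The size runs from negligible to material, depending on a share that the documents do not supply.

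**The case against.** **The gap is narrow.** A reader might infer that every short Grade 4 neutropenia with a confirmed infection now escapes. The list does not support that. The fever item sets no lower bound on ANC, so it covers Grade 4. An infection of Grade 3 or higher after supportive care counts as a non-hematologic toxicity, and recurrence counts in its own right. This objection stands and sets the scope of the point.

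**A Grade 4 count usually passes through Grade 3.** The list counts reactions observed in the window and does not say that only the peak grade is scored. If the infection is present during a Grade 3 phase, an assessor could apply the infection item. That reading is possible, but the protocol does not state it. Two identical subjects could then be scored differently, so it is a reason to clarify the list and not an answer to the gap.

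**DLT counts do not alone decide escalation.** Sections 3 and 18 and the Study Summary let the sponsor and investigators adjust doses or end escalation, and a passed level permits the next dose without compelling it. This is correct. Discretion may limit the harm, but it does not repair the scoring rule or the MTD definition built on it.

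**No rate is available.** Section 1.5 mentions no infection with its two Grade 4 cases, so it does not show that the unscored combination is common at higher doses. This stands too. On the other side, treatment with G-CSF and a time limit that runs from symptomatic treatment plausibly make short Grade 4 episodes more frequent.

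**The extended trial is fixed at 2.0 mg/kg Q2W.** Its dose therefore does not depend on this gap. What is exposed is the MTD and any recommended dose taken from the remaining escalation.

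**Conclusion.** The point holds in its narrow form. The July 2017 list, read as written and with an episode scored at its peak grade, gives no DLT for a short, non-recurring Grade 4 neutropenia with a confirmed infection below Grade 3, no qualifying fever and no other DLT. It gives a DLT for Grade 3 neutropenia with that same infection. The list before July 2017 counted both, and the protocol gives no reason for the change in the infected case.

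The consequence is a possible upward bias in the MTD of unknown and perhaps small size. A reader might go further and infer that the MTD is biased by a definite amount. The documents do not support that, because every probability above rests on assumed rates.

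**What to change.** The sponsor and investigators should reconcile the Grade 4 neutropenia item and the infection item in the Study Summary, section 3 and section 18, so that DLT scoring cannot fall as the neutropenia grade rises. They should state whether an episode is scored at its peak grade. The choice of rule is theirs, because a DLT also triggers discontinuation and later dose reduction.

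The reconciled list should then be applied to any subject evaluated under version 6.0. The protocol shows none: its data end on July 1, 2017, and that version is dated July 4, 2017.

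The cost is a few words in three copies of the list, a check of any affected subjects, and possibly a few more events counted as DLTs.
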